#### Use of NSAIDs

Ibuprofen (300 mg each capsule with sustained release) will be recommended as rescue medication, in cases who experience intolerable pain. In cases of intolerance or unresponsive to ibuprofen, other tolerable and unresponsive non-steroidal anti-inflammatory drugs (NSAIDs) could be used. The patients will be asked to record the name and dosage of NSAIDs they use during the course of the clinical trial in a headache diary.

#### Adverse Events

Acupuncture-related side effects, including serious pain, bleeding, subcutaneous hemorrhage, fainting, palpitation, and local infections, among others, will be recorded after each treatment. Additionally, adverse reactions to cointerventions will also be recorded in detail in the CRF during the whole study.

### Measurement of Other Outcomes

#### Needle Sensation Evaluations

Needle sensation (“deqi”) will be evaluated using the Massachusetts General Hospital (MGH) Acupuncture Sensation Scale (MASS) (26), a rubric designed for measurement of sensations evoked by acupuncture stimulation as perceived by the patient alone. Notably, patients will be required to fill in the MASS after each session of acupuncture treatment. This MASS will then be used, as a covariate, to exclude the potential influence of different needle sensation caused by different acupuncturists on the efficacy of acupuncture.

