## Methods and Analysis

### Objective

To quantitatively evaluate the extent of the effect of acupuncture treatment delivered by either a senior (high expectation) or junior (low expectation) acupuncturist in migraine patients.

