### Randomization and Allocation Concealment

Patients will be randomly assigned to either group A or B, using a computerized randomization sequence form according to the random number table method. Odd and even numbers will be allocated to the senior (group A) and junior (group B) acupuncturist groups, respectively. Sealed opaque envelopes, with patients screening sequence numbers and group names printed on the outside and inside, respectively, will be used for the allocation. All the recruited patients will be numbered consecutively and connected correspondingly to the envelopes. After the baseline observation phase, the envelopes will be opened, and patients will be randomly assigned to either of the two groups.

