### Blinding

Patients and acupuncturists will not be blinded due to the design and purpose of this study. Data collectors, outcome assessors, and data analysts will be blinded to the allocation.

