#### Evaluation of Patient's Expectations

The patient's expectation will be measured by AES (Appendix 1), including the expectation of the acupuncturist and the expectation of acupuncture therapy. Each patient will be asked to rate their expectation and confidence level for a junior and senior acupuncturist, respectively, using two opposing questions before randomization. The questions are as follows: “How much confidence do you have in senior acupuncturists to relieve your migraine symptoms?” and “How much confidence do you have in junior acupuncturists to relieve your migraine symptoms?” Each question adopts the percentile system, which is scored as summary percentile scales ranging from 0 to 100. Higher scores imply greater expectation and confidence. Besides, the other item of AES will be used to evaluate the patient's expectation of acupuncture therapy as a covariate.

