### Statistical Analysis

Intention-to-treat analyses will be performed where possible, with subgroup and sensitivity analyses performed, where necessary, to detect possible heterogeneity of the results. All data will be statistically analyzed using SPSS version 26.0 (SPSS Inc., Chicago, IL, USA). Two-tailed analyses will be conducted, with the level of statistical significance defined set at *P* < 0.05. Data from normally distributed continuous variables will be expressed as means with their respective standard deviations (SD), unless otherwise specified, whereas categorical variables will be presented as numbers and percentages. Distribution of continuous variables will first be analyzed using the Shapiro-Wilk test and normal probability plot. Next, we will perform a Student's *t*-test to determine differences between groups for normally distributed data. The nonparametric test will be used for skewed data, or on data with heterogeneity of variance or unknown distribution. Comparisons in response rates and incidence rate of adverse events between groups will be performed by Chi-square or Fisher's exact tests.

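### Needle sensation (MASS), scored after every session and so after randomisation, is named as an efficacy covariate; an arm difference adjusted for it is not the randomised senior-junior effect and does not by itself isolate expectation

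*Protocol article*

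**What the plan says.** All of the following is in the protocol article.

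- **Randomization and Allocation Concealment:** "After the baseline observation phase, the envelopes will be opened, and patients will be randomly assigned to either of the two groups". No treatment session takes place before that point.
- **Needle Sensation Evaluations:** MASS is a tool for "measurement of sensations evoked by acupuncture stimulation as perceived by the patient alone", and "patients will be required to fill in the MASS after each session of acupuncture treatment". The same paragraph fixes its use in the analysis: "This MASS will then be used, as a covariate, to exclude the potential influence of different needle sensation caused by different acupuncturists". The sentence ends by naming acupuncture efficacy as the thing influenced.
- **Blinding:** "Patients and acupuncturists will not be blinded due to the design and purpose of this study".
- **Objective:** to quantify the "effect of acupuncture treatment delivered by either a senior (high expectation) or junior (low expectation) acupuncturist in migraine patients".
- **Evaluation of Patient's Expectations:** a second covariate is named, because "the other item of AES will be used to evaluate the patient's expectation of acupuncture therapy as a covariate". Table 1 schedules the AES at week 0 only, and Study Design places it before randomisation.
- **Statistical Analysis:** Student's t is the "test to determine differences between groups for normally distributed data". A nonparametric test is the alternative for skewed or heteroscedastic data, and Chi-square or Fisher's exact test is used for response and adverse-event rates. No model that could hold a covariate is named.

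**The concern.** The article treats two covariates alike although they differ in kind. The AES therapy item is measured before allocation and is a legitimate baseline covariate. MASS is measured during assigned treatment, and the article itself attributes differences in it to the acupuncturist, who is the randomised factor.

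Conditioning on a consequence of the randomised factor gives up the protection of randomisation. The part of the arm effect that passes through sensation is removed. In addition, patients in the two arms with equal MASS scores need not be alike in other respects, such as pain sensitivity or response style, that also affect headache reporting.

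This matters for interpretation. Each arm is treated by one acupuncturist, and the Limitations section accepts that the two may not needle identically. Training is the design safeguard; MASS adjustment is the only analytic one that the article offers. Readers could take a MASS-adjusted difference as expectation with technique removed, which adjustment alone does not deliver.

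**Working it through.** The point rests on no figure stated in the plan, so there is none to reproduce. It follows from the order of events and from a short piece of algebra.

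**Step 1: order of events.** Baseline phase, then envelope opened, then sessions 1 to 12, with MASS after each. MASS is therefore post-randomisation, without exception.

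**Step 2: what can move MASS.** (i) Needling technique, which the article says. (ii) Expectation, because an unblinded patient rates a subjective sensation. (iii) Stable patient traits, which may also affect headache reporting.

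**Step 3: what adjustment estimates.** Take a linear model with one summary MASS score, scaled to SD 1 within arm. This is a simplification; the article does not say how the session scores are combined.

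- MASS = a × arm + c × U + error
- Outcome (reduction in migraine days) = δ × arm + b × MASS + g × U + error

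Here arm = 1 for senior and U is an unmeasured trait with SD 1. Then:

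- Total effect (unadjusted) = δ + a·b
- MASS-adjusted arm coefficient = δ − a·c·g
- Adjusted minus total = −a × (b + c·g)
- Adjusted minus direct effect δ = −a·c·g

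So adjustment changes nothing if a = 0 (MASS does not differ by arm) or if b + c·g = 0 (MASS has no association with outcome within arm). It recovers the direct effect δ when c·g = 0 (no unmeasured common cause), or trivially when a = 0.

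**Step 4: illustration only.** The total effect is set to the planning difference in Sample Size Estimation: 3.9 − 2.7 = 1.2 days. The values of a, b, c and g are assumptions; the document gives none of them.

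| a (SD) | b (days per SD) | c·g | Direct effect, 1.2 − a·b | Adjusted, 1.2 − a(b + c·g) |
|---|---|---|---|---|
| 0 | any | any | 1.20 | 1.20 |
| 0.25 | 0.6 | 0 | 1.05 | 1.05 |
| 0.5 | 1.2 | 0 | 0.60 | 0.60 |
| 0.5 | 0 | +0.5 | 1.20 | 0.95 |
| 0.5 | 0 | −0.5 | 1.20 | 1.45 |
| 0.5 | 1.2 | +0.5 | 0.60 | 0.35 |

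With c = 0.5 and g = +1 or −1 (so c·g = ±0.5), the adjusted value lies between 0.35 and 1.45 days against a true total of 1.2. In the last three rows it misses the total and the direct effect alike. A simulation of 1,000,000 patients under the same model gave 0.34 to 1.45 with MASS in the model. Without it, the coefficient stayed within 1.19 to 1.22 in every scenario.

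**Step 5: the expectation reading.** Split a into a technique part and an expectation part, a = aT + aE. Even with c·g = 0, adjustment removes aT·b + aE·b, and the second term belongs to the expectation effect. For example, aE = 0.25 with b = 1.2 (again assumed) loses 0.25 × 1.2 = 0.30 days of it. Conversely, any technique difference that acts on headache without changing reported sensation stays in the adjusted coefficient.

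**The case against.** **The primary comparison is not shown to be affected.** The Statistical Analysis section plans unadjusted tests, needle sensation is listed under other endpoints in Outcome Measures, and nothing places MASS in the primary model. This stands. A reader might infer that the primary result is biased by design; the document does not support that. It does not remove the point, because the covariate sentence refers to efficacy, carries no exploratory label, and nothing elsewhere keeps MASS out of the efficacy comparisons.

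**Removing the sensation pathway may be the aim.** The Introduction and Discussion centre on expectation when both acupuncturists follow one procedure, and the Discussion notes that expectation and practitioner capability are often mixed. On that reading, losing the part carried by technique-driven sensation is intended and is not bias in itself. This also stands, and it would be too strong to say that a direct effect can never be estimated. What remains is that the estimate needs an assumption that randomisation does not secure, and that expectation-driven sensation is removed with the rest.

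**The two acupuncturists are trained to needle alike, so MASS may not differ.** In that case there is no distortion, as the first row of the table shows. But the covariate is then of no use for its stated purpose, and unblinded patients could still report different sensation under identical needling.

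**An analysis plan not shown may supply the model.** It may, so the missing model is not the complaint. The use of a post-randomisation score as a covariate is already fixed in this article.

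**Conclusion.** The point holds in limited form. As written, the article commits to adjusting an efficacy analysis for a self-reported consequence of the randomised factor. The adjusted difference is not the randomised senior-junior effect. It is a direct effect only if MASS and headache outcome have no unmeasured common cause, and even then it may omit part of the expectation effect. MASS adjustment therefore cannot by itself separate expectation from technique.

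Direction and size cannot be derived from the document. The range of 0.35 to 1.45 days around 1.2 illustrates the mechanism under assumed coefficients and is not an estimate for this trial. There is no effect at all if MASS does not differ by arm or is unrelated to outcome.

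A reader might also infer a loss of power for the planned test. That does not follow, because a t-test without MASS is untouched by this adjustment.

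**What to change.** Replace the covariate sentence under Needle Sensation Evaluations, and carry the same wording into the Statistical Analysis section and any separate analysis plan:

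1. The primary and secondary efficacy comparisons between senior and junior groups do not include MASS.
2. Any covariates in those comparisons are measured before randomisation, such as the AES therapy item already named.
3. MASS is reported by arm as a check on uniform needling, with the caution that unblinded expectation may also shift it.
4. Any MASS-adjusted result is labelled an exploratory mediation analysis. It states the effect that it targets, the assumption of no unmeasured common cause of MASS and outcome, and the possibility that expectation acts through MASS.

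The cost is a change of wording, best made before allocation is revealed to the analysts. Data collection, visits and sample size are unchanged.

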#### Evaluation of Patient's Expectations

The patient's expectation will be measured by AES (Appendix 1), including the expectation of the acupuncturist and the expectation of acupuncture therapy. Each patient will be asked to rate their expectation and confidence level for a junior and senior acupuncturist, respectively, using two opposing questions before randomization. The questions are as follows: “How much confidence do you have in senior acupuncturists to relieve your migraine symptoms?” and “How much confidence do you have in junior acupuncturists to relieve your migraine symptoms?” Each question adopts the percentile system, which is scored as summary percentile scales ranging from 0 to 100. Higher scores imply greater expectation and confidence. Besides, the other item of AES will be used to evaluate the patient's expectation of acupuncture therapy as a covariate.

### Statistical Analysis

Intention-to-treat analyses will be performed where possible, with subgroup and sensitivity analyses performed, where necessary, to detect possible heterogeneity of the results. All data will be statistically analyzed using SPSS version 26.0 (SPSS Inc., Chicago, IL, USA). Two-tailed analyses will be conducted, with the level of statistical significance defined set at *P* < 0.05. Data from normally distributed continuous variables will be expressed as means with their respective standard deviations (SD), unless otherwise specified, whereas categorical variables will be presented as numbers and percentages. Distribution of continuous variables will first be analyzed using the Shapiro-Wilk test and normal probability plot. Next, we will perform a Student's *t*-test to determine differences between groups for normally distributed data. The nonparametric test will be used for skewed data, or on data with heterogeneity of variance or unknown distribution. Comparisons in response rates and incidence rate of adverse events between groups will be performed by Chi-square or Fisher's exact tests.

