### Sample Size Estimation

There is no available reference of clinical trials regarding the effect of patients' expectations of different acupuncturists on acupuncture-based migraine treatment so far. Our clinical experience and results from preliminary experiments indicate that the reduction number of migraine days was 3.9 ± 2.49 in the senior acupuncturist group, compared to 2.7 ± 3.45 days in the junior acupuncturist group at weeks 4–8 of treatment. PASS software version 15 was used to calculate the sample size, based on 80% power to detect a significant difference (α = 0.05, two sided), and with an excepted dropout rate of ~20%, target enrollment was set at 156 patients (78 patients in each group).

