#### Primary Outcome Measurement

The primary outcomes will comprise changes in the mean number of migraine days and the frequency of migraine attacks per 4 weeks cycle, compared to those at baseline.

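### The protocol promises covariates that its named between-group tests cannot take, and it subtracts baseline instead of adjusting for it

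*Protocol article*

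**What the plan says.** - **Outcome.** Primary Outcome Measurement defines migraine days and attack frequency per 4-week cycle as changes "compared to those at baseline".
- **Tests.** Statistical Analysis gives a t-test "to determine differences between groups for normally distributed data", an unnamed nonparametric test for skewed or heteroscedastic data, and Chi-square or Fisher's exact tests for rates. The article mentions no regression, ANCOVA or mixed model.
- **Covariates.** Evaluation of Patient's Expectations treats the "expectation of acupuncture therapy as a covariate". Needle Sensation Evaluations gives MASS, completed after every session, the same role, in order to remove the influence of differing needle sensation between the acupuncturists.
- **Population.** "Intention-to-treat analyses will be performed where possible, with subgroup and sensitivity analyses performed, where necessary".
- **Planning figures.** Sample Size Estimation reports that "the reduction number of migraine days was 3.9 ± 2.49 in the senior acupuncturist group". For the junior arm it gives a mean of 2.7 days with SD 3.45. The calculation is "based on 80% power to detect a significant difference (α = 0.05, two sided". An allowance of about 20% for dropout is stated, and the target is 78 per arm, 156 in total.

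**The concern.** Two parts of the protocol describe different analyses. One promises covariate adjustment; the other fixes tests with no place for a covariate. Without a reconciled statement, whether the primary result is adjusted, and for what, could be settled after the data are seen.

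The two covariates also differ in kind. The AES therapy item is collected before randomisation and can safely enter the primary model. MASS is recorded after each treatment session and may itself be affected by which acupuncturist gave the treatment. Adjusting for it changes the question and can bias the comparison of arms.

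Precision is also at stake. A t-test on change forces the baseline slope to 1, whereas an adjusted model estimates it. The baseline diary value is already collected in every patient, so the information is at hand but is not used as well as it could be.

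**Working it through.** **1. The passages side by side.** A two-sample t-test and a two-sample rank test take one outcome and one grouping factor. MASS and the AES item therefore cannot be covariates in either. The text of the two covariate sections and of Statistical Analysis cannot all describe the same primary analysis.

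**2. The plan's own sample size.** Inputs from Sample Size Estimation: difference 3.9 − 2.7 = 1.2 days; SDs 2.49 and 3.45; two-sided α 0.05; power 80%; dropout about 20%.

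- Mean variance: (6.2001 + 11.9025)/2 = 9.0513, so the SD is 3.01 and the standardised effect 1.2/3.01 = 0.40.
- n per arm = 2 × 9.0513 × (1.960 + 0.842)² / 1.2² = 98.7, so 99. Divided by 0.8 this is 124 per arm, 248 in total.

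The stated 78 per arm (156) is not reproduced. That is a separate matter and is used here only to set the starting power.

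**3. Power of the t-test on change.** Evaluable per arm: 78 × 0.8 = 62.4, taken as 62.

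- Noncentrality = 1.2 / √(2 × 9.0513/62) = 2.221.
- Power from the noncentral t distribution = 59.6%, about 60%.

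**4. Gain from baseline adjustment, equal variances.** Let ρ be the correlation between baseline and follow-up. The documents give no value, so 0.3 to 0.7 is an assumption.

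- Var(change) = 2σ²(1 − ρ); Var(ANCOVA) = σ²(1 − ρ²); ratio = (1 + ρ)/2.
- The noncentrality becomes 2.221/√ratio.

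| ρ (assumed) | Variance ratio | Noncentrality | Power, 62 per arm |
|---|---|---|---|
| 0.3 | 0.65 | 2.755 | 78% |
| 0.5 | 0.75 | 2.564 | 72% |
| 0.7 | 0.85 | 2.409 | 67% |

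Reaching 80% at 62 per arm would need ρ of about 0.26 or less (normal approximation). With no dropout at all (78 per arm) the figures would be 70% unadjusted and 87%, 82% and 77% adjusted, but the plan itself expects dropout.

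**5. Sensitivity to the equal-variance assumption.** Let k be baseline SD divided by follow-up SD. The ratio is then (1 − ρ²)/(1 + k² − 2ρk). For k = 0.7 (assumed):

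| ρ | Ratio | Power, 62 per arm |
|---|---|---|
| 0.3 | 0.91/1.07 = 0.85 | 67% |
| 0.5 | 0.75/0.79 = 0.95 | 62% |
| 0.7 | 0.51/0.51 = 1.00 | 60% |

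In the last row the true slope ρ/k is exactly 1, so the change score is already the optimal adjustment and nothing is gained. A baseline SD larger than the follow-up SD would give a larger gain than step 4 shows.

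**The case against.** **The analysis is valid as written.** A reader might infer that the plan ignores baseline or leaves chance imbalance uncorrected. The documents do not support that: the outcome is a change score, so the observed imbalance is removed with a slope of 1. In a randomised trial the t-test on change is unbiased. This stands, and the baseline part of the point is about efficiency only.

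**Complete-case analysis is not stated.** A reader might also infer that the t-test is run at one visit and drops everyone who misses it. The article names intention-to-treat, although qualified, fixes no single visit in Primary Outcome Measurement, and never mentions complete cases. Handling of missing data is commonly left to a fuller document. No claim is made on this.

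**An adjusted analysis may be intended.** The covariate sections suggest so, Statistical Analysis does not call its list exhaustive, and a model may be specified elsewhere. That softens the contradiction without removing it: this document names the tests and promises covariates that those tests cannot use.

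**The gain is uncertain.** It rests on an unstated correlation and on unstated variances. Eligibility at 2–8 attacks per month restricts the baseline range, which could make the baseline SD the smaller one. This stands and is why step 5 is shown.

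**Conclusion.** The point holds as an inconsistency to reconcile and an improvement worth making. It does not show that the primary test is invalid.

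The mismatch between the promised covariates and the named tests rests on the text alone and needs no assumption. The size of the precision gain does need assumptions: with equal variances and ρ between 0.3 and 0.7, adjustment adds roughly 7 to 18 percentage points of power at 62 per arm; with a baseline SD 0.7 times the follow-up SD, the gain runs from about 7 points to nil.

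It would be tempting to conclude that adjustment repairs the trial's power. In none of the cases tabulated does it reach 80%. The main cause of the shortfall is that the stated sample size does not follow from its own inputs.

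**What to change.** 1. In Statistical Analysis, replace the between-group t-test for the two primary outcomes with a baseline-adjusted model in all randomised patients: ANCOVA, or a mixed model across the 4-week cycles. Terms: arm, the baseline value of that outcome and the pre-randomisation AES therapy-expectation score. Report the adjusted difference with its 95% CI.
2. If a single cycle is to carry the primary comparison, the sponsor should name it explicitly. Primary Outcome Measurement names none, and this point does not choose one.
3. Say how the model will be checked or adapted if the outcomes are skewed, since the section already foresees that.
4. Amend Needle Sensation Evaluations so that MASS is used only in a labelled secondary or mediation analysis, and align the AES wording with the new model.

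The cost is a change of wording before the unblinded analysis and one degree of freedom per covariate. All variables are already collected, and the SPSS version named in the protocol can fit either model. The sample size needs its own recalculation; this change does not replace it.

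### The planning SDs make a switch to a nonparametric test likely, and that test neither tests nor estimates the difference in mean migraine days

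*Protocol article*

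**What the plan says.** The Statistical Analysis section of the protocol article checks the distribution of continuous variables first, with Shapiro-Wilk and a normal probability plot. It compares groups by Student's t-test if the data are normal, and otherwise follows this rule: "The nonparametric test will be used for skewed data, or on data with heterogeneity of variance or unknown distribution". It names neither the nonparametric test nor the check for unequal variances.

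Sample Size Estimation plans on a comparison of means: "the reduction number of migraine days was 3.9 ± 2.49 in the senior acupuncturist group, compared to 2.7 ± 3.45 days". The Objective is "To quantitatively evaluate the extent of the effect of acupuncture treatment" delivered by a senior or a junior acupuncturist. Primary Outcome Measurement defines the outcomes as changes from baseline in mean migraine days and in attack frequency per 4-week cycle.

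**The concern.** The trial asks how many migraine days separate the arms and is sized on a difference in means. Its analysis rule leaves the mean comparison when the variances differ, and the planning figures themselves have clearly different variances. The sample size therefore rests on inputs under which its own t-test is probably not the analysis performed.

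A rank-sum test is no answer to unequal variances. It asks whether a patient in one arm tends to rank above a patient in the other. With different spreads, that is not the same as asking whether the means are equal. At stake are which quantity the primary P value refers to, whether the data choose that quantity, and, if the data are also skewed, the error rate for a difference in mean days.

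**Working it through.** **Inputs from the article.** Means 3.9 and 2.7 days (difference 1.2); SDs 2.49 and 3.45; two-sided α 0.05; 78 enrolled per arm; dropout about 20%, so 78 × 0.8 ≈ 62 evaluable per arm.

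**Assumptions, because the article gives no figure.** Levene's test (mean-centred) at 0.05 as the variance check; Shapiro-Wilk at 0.05 in either arm; Mann-Whitney as the nonparametric test; normal data, or gamma-shaped data with a stated skewness in either direction.

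**The plan's own figure.** Pooled variance = (2.49² + 3.45²)/2 = 9.05. With n = 2 × 9.05 × (1.960 + 0.842)²/1.2², n ≈ 99 evaluable per arm, or 99/0.8 ≈ 124 enrolled per arm. The stated 78 is not reproduced. That is a separate matter; here it only explains why power at 62 per arm is about 60%.

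**Step 1: would the variance condition fire?** Variance ratio = (3.45/2.49)² = 1.92. If the trial observed exactly these SDs, the F test would give p = 0.012 at 62 per arm and p = 0.005 at 78. Allowing for sampling variation with normal data, Levene's test rejects in about 65% of trials at 62 per arm and 75% at 78.

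**Step 2: would the whole rule fire?** At 62 per arm, with Shapiro-Wilk added, it fires in about 69% of trials with continuous normal data. It fires in 76% if values are rounded to whole days, 81–83% at skewness 0.5 and about 99% at skewness 1.

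**Step 3: error rate with equal means.** SDs 2.49 and 3.45, 62 per arm, nominal 5%. There were 20,000 simulated trials per shape and direction for the single tests and 4,000 for the full rule. Ranges cover both directions of skew.

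| Shape | Rank-sum rejects | Full rule rejects | Welch rejects |
|---|---|---|---|
| Normal | 5.2% | 5.7% | 4.9% |
| Skewness 0.5 | 5.8% | 5.2–5.7% | 5.0–5.1% |
| Skewness 1 | 7.6–7.7% | 7.6–7.9% | 4.8–5.0% |
| Skewness 1.4 | 11.4% | not run | 4.9–5.2% |
| Skewness 1.5 | 11.9–12.3% | 11.6–12.1% | 4.9–5.1% |

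Other runs at skewness 1.4 gave 10.5% and 10.8% for the rank-sum test. Student's t-test also stayed at about 5% in all these shapes, because the arms are of equal size.

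**Step 4: error rate with identical arms.** If both arms share one distribution, the full rule rejects in 4.8–5.8% of trials, from normal data up to skewness 2.

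**Step 5: power for 1.2 days at 62 per arm, skewness 1.** The full rule gives 77% or 49%, depending on the direction of skew; Welch gives about 60% in both. This mirrors step 3. When the means are equal, a long upper tail makes the arm with the smaller SD tend to rank higher, and a long lower tail does the opposite. The rank test adds that shift to, or takes it from, the difference in means.

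**The case against.** Four points on the other side have force.

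- **The switch is not certain.** A reader might infer that the planning SDs will trigger the rule. On the assumed check, about one trial in three would not fire on variance. The SDs come from clinical experience and preliminary experiments of unstated size, so the ratio of 1.92 is itself uncertain. They also say nothing about skew. This stands: the switch is likely, not assured.
- **The false-positive rate is not generally inflated.** A reader might infer that the rule breaks the 5% level. With identical arms it does not, and with symmetric data and unequal SDs the rank test is at about 5%. Inflation needs unequal spread and clear skew together with equal means, that is, an acupuncturist who changes the spread of response but not its mean. This stands and limits the claim.
- **An estimate in days may still be reported.** A reader might infer that the trial would end with a P value and no effect in days. The article does not say so. It states which test gives the P value, and an unseen analysis plan may provide estimates and intervals. It also names needle sensation and therapy expectation as covariates, so some adjusted analysis seems intended. What remains is that an estimate in days printed beside a rank-test P value would not be what that P value tests.
- **The test is unnamed.** Reading it as a rank-sum test is an inference, though the natural one for two independent groups.

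None of this defends the clause on unequal variances. It is a stated rule, not a missing detail, and unequal variances alone give no reason to leave the comparison of means: Welch's test handles them directly.

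**Conclusion.** The point holds as a badly chosen rule that should be changed before analysis. If the planning SDs are about right, the primary comparison more likely than not leaves mean migraine days: about 65% of trials on variance alone and about 69% or more under the full rule, at 62 per arm with the assumed checks. It then no longer tests the quantity that defines the objective, the primary outcome and the sample size.

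The error-rate consequence is conditional. It is negligible without skew or with identical arms. With unequal spread and equal means, it is about 8% at skewness 1 and about 11% at skewness 1.4. The skewness values are assumptions, as the article gives none.

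**What to change.** Delete the pre-test switching rule for the primary and other continuous endpoints. Name one primary analysis: the difference between arms in mean change, in days (or attacks), with a 95% confidence interval, from a linear model adjusted for the baseline value with heteroscedasticity-robust standard errors. Report Welch's t-test as the unadjusted check and the rank-sum test as a sensitivity analysis. Shapiro-Wilk and the probability plot can stay as description, without deciding the test.

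Such a model can also take the pre-randomisation therapy-expectation item that the article wants as a covariate, which neither a t-test nor a rank-sum test can. Needle sensation is measured after randomisation, so whether it belongs in the primary model is a separate question.

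The cost is a short rewrite of the Statistical Analysis section and a little more analysis work. Power may be lower than with a rank test for some directions of skew: at skewness 1, about 60% for Welch against 77% for the switching rule in one direction, but 60% against 49% in the other.
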